**3.4 Planned Interventions:**

*i) Experimental Group 1*: OCfighter ([www.ccbt.co.uk](http://www.ccbt.co.uk/)) is a commercially produced cCBT programme for people with OCD. OCfighter consists of a 9 step CBT approach (focussed on exposure and response prevention) to help people with OCD to design, carry out and monitor their treatment and progress. Participants randomised to OCfighter will be given an access ID and password to log into the system and will be advised to use the programme at least 6 times over a 12 week period. cCBT will be offered in one of three locations according to patient choice and local availability: (1) the patients’ own homes or that of friend and family (if they already have a computer and a broadband connection); (2) the CBT department in the clinical site where the patient is on the waiting list (if a computer in a private room operating on a weekly booking system can be provided). In this study we will actively encourage participants to use cCBT in their own home as the first option. This will maximise patient access and flexibility whilst respecting the importance of patient choice. Our experience in our ongoing cCBT trial in depression has already shown that his is by far the most preferred means of access. We will record the location of where trial participants randomised to cCBT access the internet.

Participants will also receive six, 10 minute brief scheduled telephone calls, via phone or face-to-face (depending on patient preference) from a mental health professional (total direct clinical input 60 minutes). The support offered will consist of a brief risk assessment, ensuring that they are able to and have accessed OC-Fighter, review progress and problem solve any difficulties which are impeding progress. Mental health professionals offering support to participants will have mental health training and are therefore trained in risk assessment and deliver low intensity interventions in primary care mental health but do not have specialist CBT skills. In a current HTA study of cCBT for depression (applicant [name]) we have written a detailed guide for mental health workers offering support to patients and we will adapt this for the mental health workers in this trial.

*ii) Experimental Group 2:* Bibliotherapy (Guided Self Help) will consist of a self help book ‘Overcoming OCD’: a workbook’ written by applicant [name] [7]. Participants will receive weekly guidance from a mental health professional for 1 initial session of 60 minutes (either face to face or telephone dependent on patient preference) followed by up to 10 brief (30 minute) scheduled telephone, face to face (dependent on patient preference) sessions over a 12 week period (total direct clinical input 6 hours). The role of the mental health worker will be to conduct a semi-structured interview, devise patient centred goals and explain the structure and content of the book. They will support them to use the CBT interventions described in the book, review progress, pre-empt difficulties as they arise and engage in collaborative problem solving as required. The mental health professionals supporting bibliotherapy (guided self help) will be individuals who have had mental health training but do not have specialist CBT skills.

*iii) Comparator group 3:* Our control group will be a waiting list for conventional therapist-led CBT (in both primary and secondary care settings) as specified by the commissioning brief.

**3.6 Planned inclusion/exclusion criteria:**

Our target population will be adults of 18 and above meeting DSM IV criteria for obsessive compulsive disorder (assessed using 6 OCD questions from the Mini-International Neuropsychiatric Interview (M.I.N.I.)), scoring 16 or over on the Yale Brown Obsessive Compulsive Checklist (YBOCS), and on a waiting list for therapist led CBT in either primary or secondary mental health care settings. In addition, patients must be able to read English at a level of 11 years and above. Our rationale for an inclusion threshold of 16 on the YBOCS is that this indicates a moderate level of OCD and is the cut off score used in most clinical trials. Clinical experience and previous studies which have included a consort diagram or detailed exclusion criteria suggest that only a minority of people are referred for treatment or excluded from trials with a YBOC less than 16 (e.g. 2.3% [1] 0% [15], 14% [16]). We will exclude patients, who are actively suicidal, have organic brain disease, are experiencing psychosis, who have a diagnosis (DSM IV) criteria of drug or alcohol misuse, are currently receiving a psychological treatment for OCD, or have literacy or language difficulties to an extent which would preclude them from reading written or web based materials or conversing with a health professional.

**3.7 Ethical arrangements**

This is a trial of human subjects receiving CBT interventions in innovative delivery formats. Research governance principles and ethical committee approvals bind all applicants and their institutions. We will ensure we adopt the highest standards of research conduct in this trial including involvement of user representation on the trial management group.

***Risks and anticipated benefits for trial participants and society:*** As with any comparative treatment trial, there is the potential for the new treatments (cCBT and bibliotherapy (Guided Self Help) to be less effective than established treatments. However patients will be on a waiting list for therapist delivered CBT and the proposed study will not restrict access to CBT when they reach the top of the waiting list. Although face to face CBT is recommended by NICE, the cost and complexity of this treatment means that access is problematic because insufficient treatment resources are available to meet demand. The OCTET trial will test the effectiveness and acceptability of new treatments for people with OCD who are on a waiting list for CBT and thus has the potential to improve access to care for the UK population in the future. People who become at risk of suicide during the intervention will be identified and directed/referred to appropriate care pathways. All health professionals delivering interventions in the study will have already received risk assessment training and we will supplement this by trial specific risk protocol training.

To ensure that randomised patients have the opportunity to complete the 12-week trial intervention prior to being offered a CBT appointment from their service we will ask them to wait. This may mean that they may have to wait slightly longer for their scheduled CBT appointment if the waiting time in their service is less than 12 weeks. All participants will have the opportunity to receive scheduled CBT following 12 weeks of treatment or waiting if randomised to the waiting list group.

***Informing potential trial participants of possible benefits and known risks:*** Patient information sheets will be written according to current guidelines provided by the NHS Integrated Research Application System (IRAS) and will be approved by the relevant ethics committee prior to the study commencing. Patient information leaflets will provide potential participants with information about the study, including potential benefits and risks of taking part in the trial. A further discussion with the researcher about the risks and benefits of the study will be provided prior to consenting to the trial.

***Obtaining informed consent from participants:*** Waiting lists will be screened by a researcher, clinical studies officer (CSO) or clinical/admin site contact and potential participants will be sent an information pack about the study. The pack will contain an information leaflet, a tear off ‘consent to contact form’, researcher details, and an SAE. The information leaflets and consent to contact form will adhere to and will have been agreed by the relevant IRAS ethics committee. Patients may also be identified through direct referral from professionals, direct advertisement to patients or by self-referral through local public advertising (local newspapers, local interest magazines, Trust websites, posters in local GP surgeries and community centres, social media site (e.g. facebook) presenting information about the trial at local OCD self-help groups and on local radio) orvia a mailshot letter**,** sent to all patients currently on the waiting list. This letter will be sent with a copy of the patient information sheet (main trial) and consent to contact form. Participants who contact a researcher after receiving their contact details from an advertisement will then be sent a copy of the patient information sheet (main trial) and consent to contact form.Potential participants who consent to contact will be contacted by the site specific RA who will assess them for eligibility, discuss the trial and invite and answer questions. Written informed consent and baseline measures will be obtained prior to randomisation.

The OCTET research team based at the University of Manchester are keen to develop a research register containing OCTET participant contact details to give people the opportunity to take part in future research studies and be informed of OCD research findings. All participants who expressed an interest in the trial (and did not subsequently withdraw from follow-up) will be informed of the database by post and/or email. They will be given the opportunity to have their name included in the research register. Only individuals who return a completed opt-in form will be added to the register, their details will be help for 3 years.

***Management of relevant trial documentation:*** All data will be stored securely in line with local data management arrangements and accessed by the Trial Statistician. All paper records will be stored in secure storage facilities at the University of Manchester. Personal identifiable paper records will be stored separate from anonymised paper records. All electronic records will be stored on a password protected server within York Trials Unit and the University of Manchester. All contact information will be destroyed securely and immediately at the end of the trial.

***Proposed action to comply with EU directive and ‘The medicine for Human Use (Clinical Trials) regulations 2004:*** The study will be fully compliant with the EU directive and we will contact the relevant regulatory bodies in order to execute our study.

**3.8 Proposed sample size:**

Three pair-wise comparisons are planned between (i) self-managed therapy packages (cCBT v bibliotherapy), (ii) CBT waiting list and cCBT (iii) CBT waiting list and bibliotherapy.

In trials of non-pharmacological interventions it is recommended that variation between care-providers is considered in sample size estimation and statistical analysis. In this trial there could be variation by therapist (mental health workers) in the two self-managed therapies. For the comparisons of CBT waiting list with cCBT or bibliotherapy we have assumed between therapist variation in the active treatment corresponding to a partially-nested design [17]. For the comparison of cCBT v bibliotherapy the same set of therapists will "supervise" both interventions so the trial is therefore a cross-design [17]. Sample size is estimated using the methods described by Walwyn & [name] [17].

We are not aware of directly relevant estimates for intra-cluster correlation coefficient (ICC) for therapist required for sample size for comparison (ii) & (iii) or the ICC between treatments within therapist for comparison (i). We expect the ICC between treatments within therapist to be less than half the ICC between therapists. With a total sample size of 432 clients and 24 therapist (average of 6 therapists per clinical site) each with a caseload of 6 cCBT and 6 bibliotherapy clients the trial will have a power greater than 80% to detect a difference of 3 YBOC points for each comparison provided the ICC for therapist does not exceed 0.06 and the ICC for treatment within therapist does not exceed 0.015. This calculation assumes a 85% follow-up rate to 6 months (87% was achieved within [name] et al [1]), a 1.67% significance level to maintain a 5% sig level for three pair-wise comparisons, SD for the primary outcome YBOC at 6 months of 7.3 unit, a correlation between baseline YBOCS and 6 month YBOC of 0.43 [1]. In the event that the ICC for therapist is less than 0.1 and the ICC for treatment within therapist is less than 0.05 (which would represent unexpectedly large values), the power is still greater than 75%. By virtue of involving a comparatively large number of therapists the trial is therefore robust again larger ICC values for therapist.

**3.9 Recruitment strategy:**

Our trial will recruit a minimum of 432 patients with OCD across four clinical sites (assuming a 15% attrition rate, total N=368) with each site recruiting patients over a 27 month recruitment period (including the 9-month pilot phase). All sites will be recruiting from both primary and secondary care services (i.e. in some primary care services high intensity therapists offer full CBT and refer onto secondary care if patients fail to improve while in other services people with OCD are immediately referred to CBT delivered in secondary care). Referral rates for all the clinical sites for people with OCD range from between 60-100 patients per year. In a previous study of psychological treatment with OCD 76% of people referred for the study were randomised [1]. Each site has a designated site lead Manchester ([name]), Norwich ([name]), York ([name]), and Sheffield ([name]). To ensure recruitment we have checked waiting lists in both primary and secondary care in our clinical sites and waiting lists range from 4 to 18 months. Strong links are in place on all sites between clinical and academic staff and three of our four sites have an applicant currently treating people with OCD which will further enhance engagement with recruitment sites. In the lead site in Manchester we have had discussions with the MHRN regarding recruitment with this study if successful. The MHRN (NW hub) includes 6 NHS Trusts (including Manchester Mental Health and Social Care NHS Trust) serving a population of 3.45 million. We have agreed that if funded we will recruit from all 6 NHS trusts and to assist with recruitment in this large geographical area clinical support officers (CSOs) will be trained to conduct telephone eligibility interviews with potential participants. Of the 6 trusts in the NW hub we have agreement in principle from 4 of the NHS Trusts to host the research. We will also apply for adoption by the Mental Health Research Network and link with the Primary Care Research Network to assist with recruitment from PCTs in our clinical sites to ensure that we fulfil our recruitment target. We have a proven track record in recruiting to trials on time and within specified targets [1,18]. Our trial of cCBT uses the support network outlined above and is currently recruiting ahead of target. We have included support costs agreed and negotiated with services to compensate for any additional time involved in the process of recruitment. To meet our recruitment target we will need to recruit 17 patients per month across our 4 sites with a site recruitment target of 4-5 patients per month at each site.

**Attrition:** Attrition (or loss to follow up) occurs when a participants’ data cannot be collected for some reason and can lead to bias in RCTs [19,20]. Our estimate for attrition at the primary outcome point is 15%, based on the relevant literature of face to face OCD, cCBT and self help. In our previous trial of OCD [1] which compared 10 hours of telephone delivered CBT with face to face CBT we retained 94% of patients at post intervention and 90% at 6 month follow up. In a previous trial of guided self help by some of our team [21] we achieved follow up rates of 90% at 3 month follow up.

In keeping with the philosophy of an intention-to-treat analysis we will make every effort to follow people up regardless of whether they adhered to the treatment protocol. As those who do not adhere to the treatment protocol tend to be less adherent with outcome assessments, we will establish special procedures and make targeted efforts to achieve high rates of follow up and ensure we minimise differential attrition between treatment arms. We will explore the effect of any bias through a sensitivity analysis.

**3.10 Statistical analysis:**

A full statistical analysis plan for the analysis of primary and secondary outcome measures including any sub-group analyses will be prepared and presented to the TSC (Trial Steering Committee) prior to the commencement of the trial analysis. During the recruitment and follow-up period regular reports will be prepared for the TSC/DMEC on data quality.

Statistical analysis of outcome will follow intention-to-treat principles: patients will be analysed according to randomised group and outcome data will be sought and included in the analysis for all patients irrespective of completion of treatment. Preliminary statistical analysis will model the pattern of missing data in terms of baseline characteristics of patients.

Statistical analyses of the primary outcome measure, YBOC at 3 months, will be based on a mixed model analysis with random effects for therapist and covariates including baseline YBOC and variables potentially predictive of outcome including minimisation variables. This will be used to compare all three arms. Conditional on significance at a 5% level, pairwise comparisons between arms will be carried out using a Bonferroni corrected p-value. Similar analyses will be carried out for quantitative secondary outcomes. A logistic mixed model will be use to compare the percentage of patients requiring full CBT between treatment adjusted for baseline severity.

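### With three arms, the 5% overall test already allows unadjusted 5% pairwise tests; the Bonferroni step after it is valid but gives away power at no gain in familywise control

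*Protocol*

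**What the plan says.** Protocol section 3.10 fits a mixed model to YBOCS at 3 months and says of it: "This will be used to compare all three arms". The next sentence sets the rule for pairs: "Conditional on significance at a 5% level, pairwise comparisons between arms will be carried out using a Bonferroni corrected p-value".

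Section 3.8 lists the pairs ("Three pair-wise comparisons are planned between" the two packages, and each package and the waiting list) and sizes the trial at "a 1.67% significance level to maintain a 5% sig level for three pair-wise comparisons". It claims "power greater than 80% to detect a difference of 3 YBOC points for each comparison", subject to limits on the therapist correlations.

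Both devices are therefore fixed in the protocol. The only stated purpose of the 1.67% level is to hold 5% over the three comparisons. Section 3.8 does not mention the overall test, and neither section says why both are used.

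**The concern.** A 5% overall test and a Bonferroni correction are each ways of handling multiplicity. With three arms the overall test can do the whole job. If any two of the three pairwise nulls are true, all three means are equal and the global null is true. The only hypotheses to protect are then the global null and the three single pairwise nulls. A level-5% test of the first, followed by level-5% tests of the others, is a closed test, and it controls the familywise error strongly at 5%.

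On that argument, the division by three serves no need that section 3.8 states. At stake is power on every primary comparison at an unchanged sample size, in a trial whose protocol itself expects recruitment to be difficult.

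**Working it through.** **Inputs (protocol section 3.8).** N = 432 and 24 therapists, each with 6 cCBT and 6 bibliotherapy patients. That makes 144 per package and leaves 144 for the waiting list. "This calculation assumes a 85% follow-up rate to 6 months" gives 144 × 0.85 = 122.4 analysed per arm, or 5.1 per therapist and package. "SD for the primary outcome YBOC at 6 months of 7.3 unit" and "a correlation between baseline YBOCS and 6 month YBOC of 0.43" give an adjusted SD of 7.3 × √(1 − 0.43²) = 6.59 (variance 43.44). The therapist ICC is 0.06 and the ICC for treatment within therapist is 0.015. I assume two-sided tests and a normal approximation.

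**Reproducing the stated power at 1.67%** (critical value 2.394), without the overall test.

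- *Waiting list v package* (clustering in the package arm only). Variance = (43.44/122.4) × [1 + 1 + (5.1 − 1) × 0.06] = 0.3549 × 2.246 = 0.797, so SE = 0.893. Power = Φ(3/0.893 − 2.394) = Φ(0.966) = 83%.
- *Package v package* (therapists crossed with treatment). Variance = 2 × 43.44 × [v/24 + 0.94/122.4], where v is the share of variance that is specific to a treatment within a therapist. The text can be read in two ways:
  - v = 0.015: SE = 0.849 and power = Φ(1.138) = 87%.
  - 0.015 is the part shared by both treatments, so v = 0.06 − 0.015 = 0.045: SE = 0.911 and power = Φ(0.899) = 82%.

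The claim of more than 80% reproduces.

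**What the overall test adds to Bonferroni.** A pair with |z| > 2.394 forces the 2-df overall statistic to at least 2.394² = 5.73. The overall test needs 5.99. A pair that passes Bonferroni therefore nearly always passes the overall test too. In simulation the overall test costs 0.1 to 0.4 percentage points.

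**Comparing the two rules.** I simulated the three arm means, with the therapist effect shared between the packages and a 2-df Wald overall test at 5%. Ranges cover the two readings of the 0.015.

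| True situation | Quantity | Overall test + Bonferroni (plan) | Overall test + unadjusted 5% |
|---|---|---|---|
| All arms equal | Familywise error | 4.2% | 5.0% |
| Exactly two arms equal, third 3 points apart | Familywise error | 1.7% | 5.0% |
| Both packages better by 3 | Power, each v waiting list | 83% | 90% |
| One package better by 3 | Power v waiting list | 83% | 90–91% |
| One package better by 3 | Power v other package | 81.5–87.2% | 89–93% |
| Packages better by 3 and 1.5 | Power, 3-point pair | 82.9% | 85.7% |
| Packages better by 3 and 1.5 | Power, 1.5-point package v waiting list | 24% | 38% |
| Packages better by 3 and 2 | Power, 2-point package v waiting list | 44% | 60% |

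Unadjusted 5% tests without the overall test would have a familywise error of 12.2%, so the overall test must stay if Bonferroni goes.

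**Scale.** To reach 90% against the waiting list while staying at 1.67%, information would have to rise by (2.394 + 1.282)² / 3.360² = 13.51/11.29 = 1.20, or about 20% more patients and therapists.

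**The case against.** The strongest reply is that nothing here is wrong. Sections 3.8 and 3.10 agree on the corrected level, the familywise error stays below 5%, and the sample size was set at 1.67%, so the promised power is delivered. All of that stands. A reader might infer from the double device that the primary analysis is invalid, that the trial is underpowered, or that the two sections conflict. The protocol supports none of these.

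A reader might also infer that the plan pays for multiplicity twice. In form it does, but the overall test costs at most about 0.4 point. The loss is the ordinary price of Bonferroni.

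Nor does the Bonferroni step buy nothing. It gives matching simultaneous confidence intervals. It holds the error for a single truly null pair at 1.7% instead of 5%, which matters if one package works and the other does not. It also does not depend on the overall mixed-model test holding its level. These are real benefits, although the protocol claims none of them.

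Finally, the largest gains in the table are for differences of 1.5 and 2 points, whereas the protocol claims power only for 3. For a 3-point pair with the third arm midway the gain is about 3 points, because the overall test still limits the closed procedure.

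**Conclusion.** The point holds as an available improvement. For the one aim that section 3.8 states, the Bonferroni step after a 5% three-arm test is not needed. Removing it raises power for a 3-point difference by about 7 points against the waiting list and 6 to 8 points between packages when the third arm equals one of the pair, and by about 3 points when it lies midway. For a 2-point package beside a 3-point one the gain against the waiting list is 16 points. It would be tempting to say that the loss falls hardest on cCBT v bibliotherapy. The figures do not show that: the loss there is about the same as against the waiting list.

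The error-control argument needs exactly three arms and tests that hold their level. The power figures also assume two-sided tests, equal allocation, ICCs at 0.06 and 0.015, and the 6-month SD and correlation carried over to the 3-month endpoint. The statistical analysis plan was not available.

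**What to change.** Replace the sentence on pairwise comparisons in section 3.10 with:

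> If the three-arm test is significant at 5%, each pairwise comparison is tested at the unadjusted two-sided 5% level (closed test for three arms, familywise error 5%).

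Keep N = 432 and restate the power in section 3.8 for this rule. Make the change before outcomes are examined by arm.

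The cost is one sentence and a recalculation, with no change to recruitment or data collection. The trade-offs to accept openly are:

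- confidence intervals are per comparison, not simultaneous;
- the error rate for a single truly null pair rises from 1.7% to 5%, within the familywise 5%;
- error control then rests on the overall test holding its level.

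If the sponsor would rather have no overall test, Holm's step-down procedure rejects everything that Bonferroni rejects and recovers part of the gain: about 86% against the waiting list when one or both packages are better by 3 points. If simultaneous intervals are the reason for keeping Bonferroni, the protocol should say so.

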**3.3.2 Phase 2: Full RCT:**

If successful in recruiting to target in the pilot study (153 patients in 9 months) and with agreement from the HTA we will proceed seamlessly to a full RCT including a concurrent economic evaluation. This will be a multi-centre fully randomised controlled trial to evaluate 2 self managed packages (cCBT and bibliotherapy) compared to waiting list prior to therapist-based CBT.

The key objectives of our study are to determine:

1. The clinical and cost effectiveness of two self-managed CBT interventions (cCBT and bibliotherapy) compared to a CBT waiting list in the management of OCD patients in the short term at 3 month follow up
2. The clinical and cost effectiveness of self managed therapies plus conventional CBT compared to waiting list plus conventional CBT at 6 and 12 month follow up
3. Determine patient compliance and patient and health professional acceptability of the two self managed therapy packages (cCBT & GSH).

We will randomise patients to i) cCBT, ii) bibliotherapy (guided self help) or iii) CBT waiting list.

The primary outcome will be OCD symptoms as measured by the Yale Brown Obsessive Compulsive Checklist YBOCS [12] observer-report version. Secondary outcomes will include self-reported health-related quality of life (SF-36), self-reported OCD symptoms (YBOCs self-rated), generic mental health (CORE-OM), depression (PHQ9), anxiety (GAD-7), functioning (WSA), health-related quality of life (EQ5D), employment status (IAPT Employment Status questions A13 –A15), patient satisfaction (CSQ), attachment (RSQ), Perceived Criticism (PCS), expressed emotion (FEICS), patient progression through mental health service (Pathway questionnaire),patient and therapist acceptability (qualitative interviews), and % patients not improved or partially improved and requiring more intensive CBT. Participants will additionally be asked to complete a demographic questionnaire at baseline.

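### Section 3.10 carries out the pairwise comparisons only after a significant three-arm test, so a miss at 5% leaves the stated package-versus-waiting-list objective without a difference or interval

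*Protocol*

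**What the plan says.** Protocol section 3.10 fits one mixed model to YBOCS at 3 months, with therapist random effects and baseline covariates. Of that model it says: "This will be used to compare all three arms". The next step is: "Conditional on significance at a 5% level, pairwise comparisons between arms will be carried out using a Bonferroni corrected p-value". It then adds: "Similar analyses will be carried out for quantitative secondary outcomes". No sentence provides for a pairwise difference or interval when the three-arm test is not significant.

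Elsewhere the pairwise contrasts carry no condition:

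- Section 3.8 opens its design with "Three pair-wise comparisons are planned between" the three pairs of arms. It sets "a 1.67% significance level to maintain a 5% sig level for three pair-wise comparisons" and claims "power greater than 80% to detect a difference of 3 YBOC points for each comparison".
- The first key objective in section 3.3.2 is each package against the CBT waiting list at 3 months. The second is "self managed therapies plus conventional CBT compared to waiting list plus conventional CBT at 6 and 12 month follow up".
- Section 3.3.2 also says that the 3-month time point will allow short-term effectiveness against the waiting list to be estimated.

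**The concern.** The condition in section 3.10 attaches to carrying out the comparisons, not only to calling them significant. A three-arm test says that some arm differs. It does not say which package differs from the waiting list, or by how much. Under the rule, a global p-value of 0.06 would leave the first key objective with no effect size and no interval, and readers may take that silence as evidence of no effect.

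There is a second consequence. If differences are reported only when the global test passes, the reported ones are a selected set, and for a package with a real effect they lie on average further from zero than the truth. This is a matter of estimation. It remains whichever p-value correction is used.

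**Working it through.** **Inputs, all from section 3.8.** SD 7.3 ("SD for the primary outcome YBOC at 6 months of 7.3 unit"); baseline correlation 0.43; 432 patients, taken as 144 per arm; 85% follow-up; 24 therapists with 6 patients in each active arm; ICC 0.06 for therapist and 0.015 for treatment within therapist; level 1.67%, taken as two-sided because the text does not say. The SD and correlation are 6-month figures while the primary time point is 3 months; they are used here as the protocol uses them.

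**Step 1: reproduce the stated power.**

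- Analysed per arm: 144 × 0.85 = 122.4. Patients per therapist per active arm: 6 × 0.85 = 5.1.
- Residual SD: 7.3 × √(1 − 0.43²) = 6.59.
- Design effect, active arm only: 1 + (5.1 − 1) × 0.06 = 1.246.
- SE, package against waiting list: 6.59 × √((1.246 + 1)/122.4) = 0.893.
- Level: 0.05/3 = 0.0167, critical value 2.394. Power at 3 points: Φ(3/0.893 − 2.394) = 83.3%.

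Other reasonable variance forms and a caseload of 6 give 80.7% to 83.3% for package against waiting list, and 80.0% to 85.6% for package against package. The protocol's claim of more than 80% reproduces.

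**Step 2: apply the section 3.10 rule.** Adjusted arm means were simulated with the variances above (1,000,000 draws), followed by a 2-degree-of-freedom global test at 5%. The true differences are assumptions, except that 3 points is the design difference. Coverage is that of the nominal 95% interval for one package against the waiting list.

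| True difference from waiting list | Global test misses | Mean difference given a pass | Inflation | Coverage given a pass |
|---|---|---|---|---|
| 3 points, both packages | 4.8% | 3.08 | +3% | about 96% |
| 2 points, both | 34.8% | 2.41 | +21% | about 96% |
| 1.5 points, both | 59.3% | 2.18 | +45% | 93% |
| 1 point, both | 80.0% | 1.94 | +94% | 86% |
| 3 points, one package only | 7.1% | 3.11 | +4% | – |
| 1.5 points, one package only | 62.9% | 2.26 | +51% | – |

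In the two one-package rows, the ineffective package has a mean difference of about 0.00 given a pass, so it is not inflated on average.

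**Step 3: what the condition buys.** With no effect anywhere, Bonferroni at 1.67% without the global test gives at least one significant pair in 4.4% of trials, so familywise error is already below 5%. Power for a 3-point difference is 83.3% with or without the condition when both packages work, and 83.1% with against 83.2% without when only one does. In every scenario tried, the condition blocks a Bonferroni-significant pair in at most about 0.6% of trials.

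**The case against.** The strongest reply is that the sentence is about testing. It speaks of comparisons with a corrected p-value and does not say that estimates are withheld. The fitted model yields the adjusted differences and standard errors whatever the global p-value, and a separate analysis plan, to which section 3.10 defers, may tabulate them. This stands in part: the differences will be computable, and sensible analysts may report them. But the protocol does more than leave a detail open. It fixes a rule on when comparisons are carried out. A plan that follows the rule inherits the problem, and one that departs from it contradicts the protocol.

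Other parts of the reply stand, and they limit the point:

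- **Error rates.** A reader might infer that the rule damages error control or power. Step 3 shows that it does not.
- **Inflation.** A reader might infer that every reported estimate is materially inflated and its interval too short. At the design difference the inflation is about 3%, and under-coverage appears only at about 1.5 points or less. Nor would the fix change the number reported in a trial that passes; it removes the selection by reporting the rest.
- **6 and 12 months.** A reader might infer that the rule certainly covers YBOCS at these time points and does most harm there. Section 3.10 names only 3 months for the primary outcome, and the secondary-outcome lists in 3.3.2 and 3.12 do not name observer-rated YBOCS at later visits. The extension rests on the sentence about similar analyses. Small later differences are plausible, because section 3.3.2 expects waiting-list patients to have had CBT by then, but the 1-point figure is an assumption.
- **Other analyses.** A reader might infer that the trial could end with no package-versus-list estimate of any kind. The economic analysis (3.11) and the logistic model for patients needing full CBT (3.10) carry no stated condition.

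**Conclusion.** The point holds as a conflict within the protocol. Section 3.10 makes the pairwise comparisons of YBOCS at 3 months, and of the quantitative secondary outcomes, depend on a global test, while 3.3.2 and 3.8 make the same contrasts the unconditional objective. Taken literally, the objective goes unanswered in roughly one trial in twenty if both packages achieve the design difference, one in three at 2 points and four in five at 1 point. Selection bias is a secondary harm and is material only at about 2 points or less.

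These figures rest on the section 3.8 inputs, a normal approximation, equal allocation and the assumed true differences. The conclusion also rests on reading the condition as written, and the protocol contains no sentence that softens it. The change should be made, but this is a fault in the reporting rule and does not call the sample size or the tests into question.

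**What to change.** Replace the conditional sentence in section 3.10 with wording such as: *All three adjusted pairwise differences, with confidence intervals, will be estimated from the three-arm model and reported for every quantitative outcome and analysed time point, whatever the result of the global test. The global test and the Bonferroni-corrected p-values govern only claims of statistical significance.* Carry the same wording into the statistical analysis plan, and state there which outcomes are analysed at 6 and 12 months.

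The cost is one sentence in each document. The estimates come from the model already planned; no patients, data or sample-size figures change, and the 1.67% level stays as it is.
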